### Research questions

Can child dental health be improved by increasing parental self-efficacy using a behaviour change intervention delivered by storybooks for two child behaviours: toothbrushing and ‘sugar snacking’? (Control versus Test group 1)Can child dental health be improved by an enhanced intervention designed to improve parental self-efficacy using a behaviour change intervention delivered by storybooks for two child behaviours: toothbrushing and control of ‘sugar snacking’ *plus* home supply of fluoride toothpaste and supervised toothbrushing with fluoride toothpaste at school? (Control versus Test group 2)Does the addition of home supply of fluoride toothpaste and supervised toothbrushing with fluoride toothpaste at school increase the effectiveness of an intervention designed to improve parental self-efficacy using a storybook approach for two child behaviours: toothbrushing and ‘sugar snacking’? (Test group 1 versus Test group 2)

For a sub-study of the main study:Does an intervention designed to improve parental self-efficacy using a behaviour change intervention delivered by storybooks for two child behaviours: (toothbrushing and ‘sugar snacking’) result in changes to parental-reported child consumption of free sugars? (Control versus Test group 1)Does the addition of home supply of fluoride toothpaste and supervised toothbrushing with fluoride toothpaste at school increase the effectiveness of an intervention designed to improve parental self-efficacy using a storybook approach with embedded BCTs for two child behaviours (toothbrushing and ‘sugar snacking’) result in changes to parental-reported child consumption of free sugars? (Test group 1 versus Test group 2)Does an intervention designed to improve parental self-efficacy using a behaviour change intervention delivered by storybooks for two child behaviours (toothbrushing and ‘sugar snacking’) result in changes to the cariogenic profile of children’s microbiota? (Control versus Test group 1)Does the addition of home supply of fluoride toothpaste and supervised toothbrushing with fluoride toothpaste at school increase the effectiveness of an intervention designed to improve parental self-efficacy using a behaviour change intervention delivered by storybooks for two child behaviours (toothbrushing and ‘sugar snacking’) result in to the cariogenic profile of children’s microbiota? (Test group 1 versus Test group 2)

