### Sub-study sample, recruitment and data collection

Parents of participants in the schools in Tayside, Scotland who are already participating in The BBaRTS trial will be sent an information pack and informed consent document for the sub-study via schools. The sub-study will seek parental consent for collection of data on food and drink intake over a 3-day period using the Intake24 multiple-pass 24-hour recall system (https://intake24.co.uk) [26] or as a paper-based 3-day food and drink diary (to be entered into Intake24 by the researchers). Children will be included in the sub-study, subject to written parental consent; and will be excluded from joining the sub-study in the absence of written parental consent. In addition to parental completion of a 3-day food and drink diary, children included in the sub-study will also have a sample of unstimulated saliva collected at baseline and study end (after 2 years). It is expected that the Scottish cohort of the trial will include around 400 children and it is anticipated that about 50 % of their parents (*n* = 200) will give consent to join the sub-study.

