#### Sub-study outcomes

Measurement of free sugars’ intake and other dietary variables.

Intake24 will be used to collect dietary information from a sub-sample of the study population. Intake 24 (https://intake24.co.uk) is a participant-completed computerised dietary recall system based on multiple-pass 24-hour recalls. In this study it will be used to collect dietary information over three consecutive days. From this, the energy intake (kcal/day) and the daily amount (g/day and percentage contribution to total energy intake) and daily frequency of intake of free sugars, the percentage contribution of specific food sources to free sugars’ intake will be derived. The intake of milk and intrinsic sugars (g/day and % energy), total sugars (g/day and % energy) intake of processed starchy foods (g/day and contribution to energy intake), intake of staple starch rich foods (staples) (g/day and % energy) will also be determined. The contribution to intakes made by defined food groups (e.g. biscuits and cakes, confectionery and drinks) will be determined.2.Profile of oral microbiota, specifically *Streptococcus mutans,* lactobacilli and other caries-related bacterial taxa.

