DNA will be extracted from unstimulated saliva samples and V1–V2 of the 16S ribosomal RNA genes of bacteria in the samples will be sequenced by means of the Illumina MiSeq platform using a dual-indexing barcoding approach. Sequencing will be performed using a 2 × 300 flow cell for paired-end sequencing. Sequences will be analysed using the mothur pipeline [31], following the MiSeq SOP. Operational taxonomic units (OTUs) will be constructed at the 98.5 % similarity level. OTUs will be identified with reference to the Human Oral Microbiome Database reference dataset [32, 33]. Distance matrices, generated with the Jaccard Index and thetaYC metric, will compare sample β-diversities based on OTUs and visualised as dendrograms and three-dimensional Principal Co-ordinates Analysis (PCoA) plots (generated in R). Analysis of Molecular Variance (AMOVA) will be performed to determine if clustering patterns seen in the PCoA plots are statistically supported by differences in the distance matrix. Differentially abundant OTUs between patient groups of interest will be identified using the LDA Effect Size (LEfSe) algorithm [34]. Proportions of mutans-group streptococci, lactobacilli, *Bifidobacteriaceae* and *Propionibacterium acidifaciens* will be compared across intervention groups using appropriate statistical tests depending on the data distribution.

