#### Method of analysis

A detailed statistical analysis plan will be prepared prior to data analysis. Comparison of the primary outcome variable between the groups will be conducted using multilevel logistic regression analysis, to produce estimates of odds ratios and confidence intervals, adjusting for baseline characteristics deemed to be potential confounding variables, and allowing for clustering effect. The closed testing principle will be used to ensure a familywise error rate of less than 5 %. If the overall null hypothesis of equality of all three groups is rejected at *α* = 0.05, then pairwise comparisons between groups will be carried out at *α* = 0.05. If the overall null hypothesis cannot be rejected, no pairwise comparisons will be carried out. The potential confounders will be specified prior to analysis, and may include deprivation, age, sex and eruption status. Comparisons of secondary outcome variables between groups will be carried out using multilevel logistic or linear regression, as appropriate. Sensitivity analyses of the possible effect of missing data will be carried out using multiple imputation techniques. Reporting of the trial will follow the Consolidated Standards of Reporting Trials (CONSORT) guidelines extension to cluster trials [35].

Independent analysis will be undertaken by psychologists not involved in the development of the books. A Delphi method will be used to validate the behaviour change techniques delivered by the intervention [36, 37].

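### The LEfSe step, one of three microbiota analyses in the sub-study, screens OTUs one by one with no error control across them, so its list alone is not evidence of an intervention effect

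*Protocol article*

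**What the plan says.** Under Research questions, the protocol article asks whether the storybook intervention will "result in changes to the cariogenic profile of children’s microbiota? (Control versus Test group 1"), and puts a parallel question for Test group 1 against Test group 2.

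Under Sub-study outcomes, the microbiota outcome is a profile that names *S. mutans*, "lactobacilli and other caries-related bacterial taxa". Sequences are grouped first: "Operational taxonomic units (OTUs) will be constructed at the 98.5 % similarity level". Three analyses follow:

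- A global test on the distance matrices: "Analysis of Molecular Variance (AMOVA) will be performed to determine if clustering patterns seen in the PCoA plots are statistically supported".
- A screen of single OTUs: "Differentially abundant OTUs between patient groups of interest will be identified using the LDA Effect Size (LEfSe) algorithm".
- A comparison of four pre-named taxa (mutans-group streptococci, lactobacilli, the *Bifidobacteriaceae* and one *Propionibacterium* species), whose proportions "will be compared across intervention groups using appropriate statistical tests depending on the data distribution".

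For LEfSe the article gives no alpha, LDA cut-off, number of OTUs or adjustment. It neither makes the screen depend on AMOVA nor calls it exploratory. Under Method of analysis, error control reads "The closed testing principle will be used to ensure a familywise error rate of less than 5" per cent. The steps described there are a global test of the three groups followed by pairwise comparisons. That section also announces a detailed statistical analysis plan, which is not available here.

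**The concern.** The sentence on LEfSe treats a flagged OTU as one that has been found to differ. In its usual form LEfSe runs a rank test on each OTU at a fixed alpha and keeps those whose LDA score exceeds a cut-off. This is general knowledge of the named method; the article does not describe it. The cut-off removes small differences but does not limit false positives over the number of OTUs screened. Grouping at 98.5% similarity will usually give many OTUs.

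If the method is followed as named, a list of differing OTUs can be expected even when the arms do not differ. Printed beside a research question about change in the cariogenic profile, such a list could be taken as an effect of the intervention. The problem does not depend on the clustering of children in schools: it is present even if all children are independent, and clustering adds to it.

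**Working it through.** **Sub-study size.** The only figure given for the sub-study is its size. About 400 Scottish children are expected, and "it is anticipated that about 50 % of their parents" will consent: 400 × 0.50 = 200, as stated. Three equal arms would have 200 / 3 ≈ 67 children each.

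**Assumptions.** The article does not give the following, so ranges were used: alpha 0.05 per OTU; 20, 50, 100 or 200 OTUs; LDA cut-off 2, 3 or 4.

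**Formula, independent tests, no LDA cut-off.** P(at least one false OTU) = 1 − (1 − 0.05)^m, and the expected number of false OTUs is 0.05 × m.

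- m = 20: 1 − 0.95^20 = 64%; expected 1
- m = 50: 1 − 0.95^50 = 92%; expected 2.5
- m = 100: 1 − 0.95^100 = 99.4%; expected 5
- m = 200: more than 99.9%; expected 10

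**Simulation with no effect and an LDA-type cut-off.** Each setting had 300 data sets of 200 children in 12 schools and three arms, with log-normal abundances and about 10,000 reads per sample. (At the main trial's average of 30 pupils per school, 400 children would be 400 / 30 ≈ 13 schools.) An OTU was flagged if the Kruskal-Wallis p was below 0.05 and log10(1 + half the range of arm means on a one-million scale) exceeded the cut-off. Chance of at least one flag with school ICC 0:

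- cut-off 2: 63% (20 OTUs), 89% (50), 99% (100), 100% (200)
- cut-off 2 with correlated OTUs: 95% (100), 98% (200)
- cut-off 3: 87% (100)
- cut-off 4: 32% (200)

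With 300 data sets, the standard error of the 32% figure is √(0.32 × 0.68 / 300) ≈ 2.7 percentage points.

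**Same data with Benjamini-Hochberg at 5% across OTUs.** When no OTU differs, the false discovery rate equals the chance of naming any OTU, so the target is 5%. The result was about 3% to 7% with ICC 0. With ICC 0.01, the school-level value used in the article's sample size, and tests that ignore school, it was about 7% to 11%.

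**Limits.** The simulation imitates LEfSe and does not run the software. It compares three groups at once, whereas the research questions are pairwise. Not every combination of OTU count and cut-off is reported above, so 32% is the lowest value among those listed and not a bound.

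**The other two analyses.** AMOVA is a global test for each distance matrix and does not grow with the number of OTUs. The four pre-named taxa at 0.05 each, if independent, give 1 − 0.95^4 = 18.5%. That is above 5%, but it concerns a short list fixed in advance.

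**The case against.** A reader might infer that the sub-study answers its microbiota question by the LEfSe list, so that the question would nearly always be answered yes. The article does not support this. The outcome is defined around named caries-related taxa, and both AMOVA and the comparison of four such taxa fit a question about the cariogenic profile more directly. The LEfSe sentence does not name the trial arms as its groups, while the sentence on the four taxa does. Nothing says that flagged OTUs will be reported as intervention effects.

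A reader might also infer that false OTUs are almost certain. That needs an OTU count, an alpha and a cut-off that the article does not give. With a cut-off of 4 the chance fell to 32%.

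The strongest objection is that the absence of an adjustment is only silence in a condensed article, and that the unseen analysis plan may supply one. This lowers the weight of the point and is the main reason to rate it minor. It does not remove it. The article goes into detail here, names a specific algorithm and says what it will identify. Followed as named, that algorithm has no control across OTUs, so the analysis plan would have to add to it.

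**Conclusion.** The point holds for the LEfSe step only. That step commits to a per-OTU screen which, as named, has no error control across OTUs. AMOVA does not gate it and the closed testing does not cover it. With no effect, at least one OTU would be falsely named in about 32% to 100% of data sets over the assumed settings. Even the lowest of these is more than six times 5% (32 / 5 = 6.4). The list alone should therefore not be read as evidence of an intervention effect.

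This rests on the usual form of LEfSe, on the assumed settings and on an approximate simulation. Severity is minor: only an optional sub-study of about 200 children in one area is affected, two other microbiota analyses bear on its question, and the primary and main-trial outcomes are untouched.

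**What to change.** In the microbiota paragraph of Sub-study outcomes, or in the analysis plan, state that:

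- for any contrast between trial arms, an OTU is declared differentially abundant only if its p-value passes a Benjamini-Hochberg false discovery rate of 5% across all OTUs tested in that contrast;
- the p-values come from a test that respects the clustering of children in schools, since otherwise the stated rate does not hold;
- the LDA score is used to rank or display the OTUs that pass;
- all other LEfSe output is exploratory;
- AMOVA and the four pre-named taxa carry the inference on the cariogenic profile.

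This takes a few sentences and a little code, and needs no new data or change of design. The price is that fewer OTUs will be declared, with some loss of power for weak differences in single OTUs.

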### Randomisation

Following the collection of consent forms from parents and collection of baseline dental and questionnaire data, schools will be randomised to Test group 1 (test books only), Test group 2 (test books and fluoride toothpaste), or Control (control books). The study flow in each group is presented in Fig. 1.

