#### Sample size

Previous study and pilot study data on similar populations have shown that there is likely to be virtually no caries in first permanent molars at baseline, and most teeth will be unerupted [15]. As the study is cluster randomised, the intra-cluster correlation coefficient (ICC) must be considered when calculating sample size. Few estimates of school-level ICC are available for dental data, so a value of 0.01 was used, based on unpublished data collected by the authors. To allow for participant dropout and non-consent, it is assumed that an average of 30 pupils per school will participate and have primary outcome data available at study end. If the caries incidence in the control group is 35 %, the observed value in a previous study in a deprived population, a sample size of 19 schools per group allows detection of a reduction in caries to 25 % incidence in the test groups, with 80 % power, overall *α* = 0.05 (adjusted for multiple comparisons), and ICC = 0.01. For caries incidence in the control group of 20 % (the approximate value observed in the pilot study); the same sample size allows detection of a reduction to 12 % in the test groups. To allow for potential withdrawal of schools, one additional school will be recruited in each group; therefore, 60 primary schools will be randomly allocated to three clusters, taking area into account. If the assumption of 30 pupils per school holds, this will give a total sample size of 1800.

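### The microbiota analyses named for the sub-study make no stated use of each child's baseline saliva sample, or of school, the unit randomised

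*Protocol article*

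**What the plan says.** - **Research questions.** For Control versus Test group 1, the sub-study asks whether the intervention will "result in changes to the cariogenic profile" of the children's microbiota. A parallel question compares Test group 1 with Test group 2.
- **Sub-study sample, recruitment and data collection.** Each child is to give "a sample of unstimulated saliva collected at baseline and study end (after 2 years". The Scottish cohort is put at around 400 children, and "it is anticipated that about 50 % of their parents (*n* = 200) will give consent to join the sub-study".
- **Sub-study outcomes.** Sequencing and bioinformatics are set out in detail, down to the OTU similarity threshold (98.5%). Three analyses are named: AMOVA on between-sample distances; LEfSe between groups of interest that are not defined; and a comparison of mutans-group streptococci, lactobacilli, *Bifidobacteriaceae* and *Propionibacterium acidifaciens*, whose proportions "will be compared across intervention groups using appropriate statistical tests depending on the data distribution". The section does not say which visit is analysed, and does not mention baseline, change or school.
- **Randomisation.** "schools will be randomised to Test group 1 (test books only), Test group 2 (test books and fluoride toothpaste), or Control (control books", with stratification by recruiting area.
- **Method of analysis.** The primary outcome gets multilevel logistic regression with covariate adjustment, and secondary outcomes get multilevel regression. Sub-study outcomes have their own heading and methods and are not mentioned here. A detailed statistical analysis plan is to follow.

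**The concern.** The question and the sampling are longitudinal, but the named analyses, in their standard form, compare groups of single samples. The only stated criterion for choosing the taxon tests is the shape of the distribution. That criterion does not lead to a model containing the child's baseline value or the school.

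Two things are at stake. First, few schools supply the sub-study, so arms may differ in microbiota at the start by chance. A study-end comparison carries part of that difference into the result, although the sample that would correct it is already planned. Second, if children are treated as independent when schools were allocated, standard errors are too small.

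The text also leaves open whether both visits enter one AMOVA or LEfSe run. With equal numbers at each visit, no arm difference *d* before treatment and *d* after, the pooled arm difference is (0 + *d*)/2 = *d*/2.

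**Working it through.** **1. The plan's own figure.** No power or precision figure is given for the microbiota sub-study. The main-trial calculation, which supplies the ICC and school size used below, reproduces. For 35% versus 25%, 80% power and two-sided α = 0.05/3, with pooled variance under the null and no continuity correction, n = 439 per group. The design effect is 1 + (30 − 1) × 0.01 = 1.29. Then 439 × 1.29 = 566, and 566/30 = 18.9, so 19 schools per group as stated.

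**2. Structure of the sub-study.** The school size comes from the Sample size section, where "it is assumed that an average of 30 pupils per school will participate and have primary outcome data available at study end".
- Schools: 400/30 ≈ 13, or 4 to 5 per arm.
- Children: 200/3 ≈ 67 per arm; 200/13.3 ≈ 15 per school.
- Sensitivity: the abstract's 2000–2600 children in 60 schools is 33 to 43 per school, giving about 9 to 12 Tayside schools, 3 to 4 per arm.

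**3. Chance difference between two arms at baseline**, in SD units: √(2/67 × DE), with DE = 1 + (15 − 1) × ICC.
- ICC 0.01 (the protocol's caries value): DE = 1.14; √(2/67 × 1.14) = 0.18.
- ICC 0.05 (assumed): DE = 1.70; √(2/67 × 1.70) = 0.23.

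**4. Precision from baseline adjustment.** Residual variance is multiplied by 1 − r², where r is the within-child correlation over 2 years. The documents do not give r.
- r = 0.3: 0.91, a 9% cut, worth 1/0.91 = 1.10 times the children.
- r = 0.6: 0.64, a 36% cut, worth 1/0.64 = 1.56 times the children.

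**5. Simulation with no true effect.** Two arms of 4 schools with 17 children each (68 per arm), a normally distributed outcome such as a transformed taxon proportion, school effects correlated 0.8 over time, r = 0.3 and 0.7, and 3000 runs per setting. Entries are rejection rates at a nominal 5%, as the range over the two values of r. The last column is the share of runs with a baseline gap of at least 0.3 SD in either direction.

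| School ICC | Child level, 2-year only | Child level, baseline-adjusted | School level, with or without baseline | Gap ≥ 0.3 SD |
|---|---|---|---|---|
| 0 | 4.4–5.7% | 4.9–5.2% | 4.6–5.1% | 7.5–8.3% |
| 0.01 | 6.4–7.2% | 5.9–6.0% | 4.9–5.4% | 10.0–11.2% |
| 0.05 | 14.6–15.0% | 11.2–12.2% | 4.6–5.5% | 18.5–18.9% |
| 0.10 | 22.6–22.7% | 16.5–18.6% | 5.0–5.6% | 28.2–29.0% |

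Across settings, adjustment lowers the SD of the estimated arm difference from 0.17–0.28 to 0.12–0.23. In runs where one arm starts at least 0.3 SD higher, the 2-year-only difference averages 0.12–0.33 SD, against about 0–0.13 SD after adjustment.

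The table separates the two problems. The excess false positives come from ignoring school: baseline adjustment alone lowers them but does not remove them, and school-level tests stay near 5% either way. Baseline adjustment gives precision and protection in the particular sample drawn. AMOVA and LEfSe themselves were not simulated.

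**The case against.** The other side has four good arguments.

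- **The text never says the tests are unpaired.** A reader might infer that the plan commits to discarding the baseline sample, or to pooling the visits. It commits to neither: the visit and the LEfSe groups are undefined and the taxon tests are left open. This stands, so the point is about what is not stated, not about a declared unpaired analysis.
- **The analysis plan may settle it.** Adjustment for baseline is ordinary content for an analysis plan, and a journal article condenses. This stands in part. The section nevertheless goes as far as naming the tests, and ties one choice to distribution alone. What is named is weaker than an available alternative, so it is more than missing detail.
- **A study-end contrast answers the question.** A reader might infer that it is biased, or fails to address change. The question is labelled as a comparison between arms, and under randomisation a study-end contrast is unbiased on average. This stands.
- **Chance imbalance is not a source of excess false positives.** A standard error that respects the allocation already covers it. This stands too: the inflation belongs to clustering.

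It would also be wrong to treat the saliva as already in hand. Under Trial status the trial is still recruiting, so both samples are planned.

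**Conclusion.** The point holds in a limited form. The microbiota analyses, as named, make no stated use of a baseline sample the trial plans to collect, and none of the school allocation.

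- **Baseline.** Leaving it out costs about 9–36% of residual variance for an assumed within-child correlation of 0.3–0.6, and leaves the result exposed to a chance baseline difference with SD about 0.18 (ICC 0.01) to 0.23 (assumed ICC 0.05).
- **School.** Child-level 2-year tests that ignore it would have a type I error of about 6–7% at ICC 0.01 and about 15% at an assumed 0.05. At the protocol's own ICC the inflation is small.

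The ICC of 0.01 was chosen for caries; no microbiota ICC or within-child correlation is given. The count of 13 schools is derived from planning figures and could be nearer 9. The primary outcome is not affected.

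**What to change.** Under Sub-study outcomes, or in the analysis plan:

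1. **Named taxa.** Model the suitably transformed 2-year proportion on arm, with the child's own baseline proportion as covariate and a random effect for school. Given the few schools, a school-level analysis of baseline-adjusted values is an alternative.
2. **Community composition.** Test arm on study-end samples adjusting for baseline composition (for example the leading baseline PCoA axes), or test the arm-by-time term with child as block. Permute arm at school level.
3. **Visits.** Do not pool the two visits in AMOVA or LEfSe, and treat LEfSe as descriptive.
4. **Timing.** Confirm that baseline saliva precedes the first book. The Randomisation section lists dental and questionnaire data as collected before allocation, but not saliva.

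The cost is analysis wording only, since both samples are already planned. Children without a baseline sample will need imputation or a missing indicator. School-level permutation is also coarse for a pairwise comparison: 4 versus 4 schools has 8!/(4! × 4!) = 70 allocations, so the smallest two-sided p is 2/70 = 0.029; 3 versus 3 has 20, so it is 2/20 = 0.10. The school count should be checked before that test is fixed.
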